### Participants, eligibility criteria, and settings

The study is conducted in 11 Tunisian medical ICUs: Rabta, Ariana, severe burns department, Zaghouan, Habib Thameur Center, Mahdia, Farhat Hached Sousse Center, Sfax, Bizerte, Tunis Urgent Medical Assistance Center, and Mahres. The recruitment period for this study is scheduled to begin on September 15, 2023 and end over one year, i.e. September 15, 2024. Are eligible for our trial, all patients aging 18 or older, admitted in ICU, who present sepsis and a decrease in MAP below 65 mmHg. According to the sepsis 3 definitions update [1], sepsis is defined as an organ dysfunction caused by a documented or suspected infection. Organ dysfunction is represented by an increase in the Sequential [sepsis-related] Organ Failure Assessment (SOFA) score of 2 points or more. Exclusion criteria are: pregnancy, surgery indication, neoplasia, circumstances where fluid restriction is the rule (acute cardiogenic pulmonary edema…).

It should be noted that sepsis is only considered for inclusion when it occurred in the ICU to minimize the interventional bias. Septic patients who started receiving fluid therapy or vasopressive agents in their original departments (emergency or others) are excluded. Patients who die before primary outcome assessment are considered treatment failure.

In accordance with ethical principles of international guidelines including the Declaration of Helsinki, Council for International Organizations of Medical Sciences (CIOMS) International Ethical Guidelines, and International Conference on Harmonization (ICH) Good Clinical Practice (GCP) Guidelines, the protocol and other relevant documents are reviewed and approved by the institutional ethics Committee of the Northern Data Protection Committee of Tunisia on 11/04/2023 (CPP_37_2022_SI_noradrénaline) (supplement document). A written and informed consent is obtained from all patients or their legal representative. In case of urgent inclusion, we opt to call the legal parents to find out who can provide oral consent—or not; after explaining the study and its objectives. If oral consent is provided, the written consent will be completed the next day.

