### Outcomes (primary and secondary)

Our Primary Outcome is the shock control defined by a composite criterion (MAP > 65 mm Hg for 2 consecutive measurements AND urinary output > 0.5 ml/kg/h for 2 consecutive hours) within 6 hours. Secondary Outcomes are: Variation of CO (the 15% threshold is considered to define an increase in CO) within 6 hours, decrease in serum lactate > 10% from baseline within 6 hours, Quantity of intravenous fluid received, Improvement of SOFA at H24, vasopressors free days, ICU stay, ventilator free days, and 28 days-Mortality.

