### Power and sample size

Herein, the major endpoint is the percentage of patients whose hypotension is restituted within 6 hours. According to the study by Permpikul C, et al (the CENSOR trial [5]), the shock control rate at 6 hours was significantly higher in the early norepinephrine group (76.1%) versus (48.4%) in the Placebo group. Consequently, the computation is performed as follows:

N per group = x

Where pA is the percentage of shock control within 6 hours in the early norepinephrine group (0.761) and pB is the percentage in the placebo group (0.484). Thus, for a targeted statistical power of at least 90% and at an alpha risk of 0.05, the size required for each arm is at least 96 patients. The desired effect size, based on the power and sample size mentioned above, was estimated at a gain of 1 hour 45 minutes from initial treatment to achieving target MAP and tissue perfusion goal.

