### Statistical analyses planned

Enrollment of at least 96 participants per group would provide a statistical power at 90% to assess the difference in the primary outcome between the two groups at a two-sided alpha error of 0.05. All primary and secondary outcomes analyses are based on the intention-to-treat principle. The primary outcome and other categorical variables are evaluated by the chi-square test or Fisher exact test, where appropriate. The independent link between early NE and shock resolution will be evaluated using proportion regression (Beta regression approach). Under violations of normality/Gaussian assumptions, we will employ the Wilcoxon-Mann-Whitney test to assess group differences for continuous variables. For the 28-day mortality analysis, time to death is calculated from date of sepsis diagnosis to date of death. Survival distributions in the two groups are estimated by Kaplan-Meier curves. Values of p less than 0.05 are considered to indicate statistical significance. All data analyses will be performed using SPSS Statistics version 20 (SPSS Inc.). Missing data will be handled using the imputation approach.

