## Discussion

In this multicenter RCT, we plan to include at least 200 patients (n = 100 per group), which is, to our knowledge, the first and largest RCT involving almost all Tunisian ICUs reported to date. During the preparation of this manuscript, the methodology diffusion via several meetings between the investigators is taking place. We plan to close the study inclusion in September 2024.

The trial’s methodology requires a certain level of attention; particularly during the first six hours. Indeed, during this time interval, the patient is enrolled in his trial group, basic data (hemodynamic parameters, echocardiography and lactate level) are collected, quantity of volume expansion is determined (while being guided by responsiveness indices and monitored by hourly intakes of MAP, diuresis, heart rate, skin recoloration time, etc…), labeling a success or failure status according to the defined endpoint composite criterion. This entire assessment will be redone at H6 in order to assess the effect of the tested action (early NE or standard care) on the stroke volume, cardiac output, LV filling pressures and on the drop in lactate. The received fluids volume over the 6 hours and the total cumulative dose of NE administered during the septic episode will be also quantified.

Concerning the fluid balance, it is now well established that a positive balance is independently associated with an increased mortality rate in septic shock [9, 10]. It makes perfect sense to restrict fluid intake by initiating vasopressors early. In fact, the CENSER-RCT [6] found that the shock was more resolved by 6 hours in the early norepinephrine group (118/155 [76.1%] vs. 75/155 [48.4%]; *P* < 0.001); yet the 28-day mortality did not differ [5]. Despite the large sample size (n = 155 per arm), this trial only included one center and did not evaluate the immediate impact on stroke volume and CO. In the current trial, we try to circumvent these two limitations.

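### The Beta regression named for the independent effect of early NE on shock control cannot be fitted to a per-patient yes/no outcome; the chi-square/Fisher primary test is unaffected

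*Protocol article*

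**What the plan says.** Under Outcomes, the protocol article makes the primary endpoint a condition that each patient either meets or does not: "Our Primary Outcome is the shock control defined by a composite criterion", requiring both a blood pressure and a urine output condition within 6 hours. The Discussion confirms the scoring, describing "labeling a success or failure status according to the defined endpoint composite criterion". The eligibility section adds a coding rule for early deaths: "Patients who die before primary outcome assessment are considered treatment failure". The sample size compares two group rates. For the treated arm it states: "pA is the percentage of shock control within 6 hours in the early norepinephrine group (0.761"). The control rate, 0.484, is taken from the same cited trial.

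The section on planned statistical analyses first treats this outcome as categorical: "The primary outcome and other categorical variables are evaluated by the chi-square test or Fisher exact test, where appropriate". The next sentence assigns a different kind of model to the same outcome: "The independent link between early NE and shock resolution will be evaluated using proportion regression (Beta regression approach"). No covariates are listed for that model. The article does not mention grouping patients into proportions, a zero/one-inflated version, or any transformation of the outcome.

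**The concern.** Beta regression is meant for a continuous response lying strictly between 0 and 1. Here the only values a patient can have are 0 and 1. The wording suggests that a percentage in a group was taken for a proportion measured on each patient.

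This is the only model that the section names for an independent effect on the primary outcome. Randomization is stratified by age and SOFA score, and the Discussion says that correlation within centres has to be controlled. The simple test does neither. If the sentence stays, the analyst will either meet a failed fit and choose another model after seeing the data, or force a fit and report an effect that is far too small.

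**Working it through.** **Inputs.** Rates 0.761 and 0.484 and 96 patients per arm (Power and sample size); two-sided 5% level ("at a two-sided alpha error of 0.05", Statistical analyses planned). The figure of 96 is used only as the stated trial size. The usual two-proportion formula at 90% power gives 63 per arm, or 70 with continuity correction, but that is a separate matter and does not affect this point.

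**Planning odds ratio.** (0.761/0.239) / (0.484/0.516) = 3.184/0.938 = 3.39.

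**Step 1: can the model be fitted as written?** With mean μ and precision φ, the Beta log-density is a constant plus (μφ − 1)·log(y) + ((1 − μ)φ − 1)·log(1 − y).
- At μ = 0.6, φ = 5 the coefficients are 2 and 1, so the value is minus infinity at both y = 0 and y = 1.
- At μ = 0.6, φ = 1 they are −0.4 and −0.6, so the value is plus infinity at both.

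There is no usable likelihood for any patient. A standard Beta regression routine (statsmodels) refuses the raw 0/1 data.

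**Step 2: the right model on the expected data.** Expected counts are 96 × 0.761 ≈ 73 and 96 × 0.484 ≈ 46 successes. Logistic regression with treatment alone gives:
- odds ratio (73/23)/(46/50) = 3.174/0.920 = 3.45; log odds ratio 1.238
- standard error √(1/73 + 1/23 + 1/46 + 1/50) = 0.315
- 95% CI 1.86 to 6.39

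**Step 3: what a forced fit would give.** This step is conditional, because the article describes no such device. The usual shift is y′ = (y(N − 1) + 0.5)/N with N = 192, which turns 0 into 0.5/192 = 0.0026 and 1 into 191.5/192 = 0.9974.

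| Same data, 73/96 vs 46/96 | Log OR (SE) | OR | Early-NE rate | Control rate |
|---|---|---|---|---|
| Observed / logistic | 1.238 (0.315) | 3.45 | 0.760 | 0.479 |
| Beta after shift | 0.599 (0.200) | 1.82 | 0.635 | 0.488 |

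The Beta log odds ratio is 0.599/1.238 = 0.48 of the logistic one. The choice of shift hardly matters: moving the values inward by 0.000001, 0.001, 0.01 or 0.05 gives odds ratios of 1.79, 1.81, 1.84 and 1.86.

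**Step 4: repeated sampling, 96 per arm, usual shift.**
- Planning rates, 300 simulated trials: mean Beta odds ratio 1.84, mean fitted early-NE rate 0.64. The two-sided 5% test rejects in 91% of trials, against 97% for logistic regression. Monte Carlo standard errors are √(0.91 × 0.09/300) = 1.7 points and √(0.97 × 0.03/300) = 1.0 point. A repeat with 2,000 trials gave 94% and 98%, with mean odds ratio 1.83.
- No effect, 0.60 in both arms: the Beta test rejects in 0.7% to 1.2% of trials across runs, against a nominal 5%.

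**The case against.** The strongest reply is that the trial's main result does not depend on this model. That stands. The primary outcome has its own valid test in the preceding sentence, so a reader who infers that the primary comparison is compromised goes further than the document supports.

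A second reply is that the attenuated odds ratio comes from a workaround the plan never mentions. That also stands. What follows from the text is that the fit fails. A failure would be noticed at once, and a distorted published estimate is only one possible consequence. Nor does the forced fit favour the treatment: it shrinks the effect and makes the test conservative, so fear of a spurious claim of benefit is unsupported.

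Third, the authors may have meant a binomial model, or a model of grouped proportions, and named it loosely. Neither is described. Grouping would not be a safe rescue either. Assume 11 equal centres with about 9 patients per arm each. The chance that a centre has no cell at 0% or 100% is (1 − 0.761⁹ − 0.239⁹)(1 − 0.484⁹ − 0.516⁹) = 0.911, so the chance of at least one such cell is 1 − 0.911¹¹ ≈ 64%. Adjustment at patient level would also be lost.

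Fourth, details of this kind may be left to an analysis plan that is not shown. Here, however, the article names a specific method, and an analysis plan could be right only by contradicting it.

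Finally, covariate adjustment is an inference from the word independent; the section lists no covariates. The reading is natural, but the point does not need it, since every calculation above uses treatment as the only predictor.

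**Conclusion.** The point holds within these limits. Beta regression is the wrong model for shock control as the article defines it and cannot be fitted to the 0/1 data. The chi-square/Fisher comparison is sound. The defect lies only in the model for the independent, by natural reading covariate-adjusted, effect.

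The failure to fit rests on the document's text alone. The size of the distortion rests on three assumptions: that someone shifts the values to force a fit, that the planning rates hold, and that 96 patients per arm are analysed. Under them the odds ratio is roughly 1.8 instead of 3.4, the early-NE rate is understated by about 0.12 (0.76 − 0.64), rejection under no effect is about 1%, and power falls by about 4 to 6 points (94% against 98%, or 91% against 97%, depending on the run). This should be fixed, but it does not threaten the trial's main conclusion.

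**What to change.** Replace the Beta regression sentence with one that names a single binary-outcome model, for example:

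> The adjusted effect of early NE on shock control (yes/no) will be estimated by logistic regression with treatment, age stratum (≤55/>55) and SOFA stratum (≤5/>5) as fixed effects and centre as a random intercept.

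The covariates are the stratification factors already used in randomization, and the random intercept deals with the centre correlation raised in the Discussion. Other binary-outcome models would also cure the defect; what matters is that one is fixed before the data are analysed. The cost is one sentence. No patients, data collection or trial procedures change, and the primary test stays as it is.

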**Fig 1 pone.0307407.g001:**
[figure not shown]
Spirit schedule of the study protocol. Once sepsis with hypotension is diagnosed in and consent is obtained, he is eligible and according to randomization he is allocated either to the early NE or placebo group. Are recorded clinical and biological data (blood gases, lactate, ionogram and renal function), basic cardiac echocardiography (stroke volume (SV), cardiac output (CO) and E/E’ ratio in addition to standard care according to SSC 2021, measurement of MAP every 15 mn and hourly monitoring of urine flow until H6. At H6: in addition to the clinical parameters of interest (MAP and diuresis), lactate levels, echo cardiographic parameters and fluid received. Clinical monitoring will be carried out until discharge in order to determine Vasopressors free days, ICU stay, ventilator free days, and 28 days-Mortality.

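### Follow-up that ends at discharge does not secure day-28 vital status, and the survival clock starts at sepsis diagnosis instead of randomisation

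*Protocol article*

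**What the plan says.** *Outcomes (primary and secondary)* closes its list of secondary outcomes with "vasopressors free days, ICU stay, ventilator free days, and 28 days-Mortality".

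The Fig 1 legend says how these are obtained: "Clinical monitoring will be carried out until discharge in order to determine Vasopressors free days, ICU stay, ventilator free days, and 28 days-Mortality". It does not say whether discharge is from the ICU or from hospital, and it mentions no contact at day 28.

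*Statistical analyses planned* sets the time origin, "time to death is calculated from date of sepsis diagnosis to date of death", and the estimator, "Survival distributions in the two groups are estimated by Kaplan-Meier curves". It states no censoring rule. It adds that "All primary and secondary outcomes analyses are based on the intention-to-treat principle" and that "Missing data will be handled using the imputation approach".

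Randomisation comes later than, or at the same time as, diagnosis. Eligible patients are those "who present sepsis and a decrease in MAP below 65 mmHg". Under Fig 1, once hypotensive sepsis is diagnosed and consent is given, "he is eligible and according to randomization he is allocated either to the early NE or placebo group".

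**The concern.** A 28-day endpoint needs each patient's status on a fixed day. Monitoring that stops at discharge ends on a different day for each patient, and for many survivors that may be before day 28. For those patients the plan ties the endpoint to data that will not contain it.

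Each way of filling the gap has a cost. Patients well enough to leave are generally at lower risk than those who stay, so censoring them at discharge breaks the independent-censoring assumption of Kaplan-Meier. Assuming they are alive leaves out deaths after discharge. Imputing their status replaces a fact that a phone call could supply. The trial expects earlier shock control in one arm and lists ICU stay as an outcome, so discharge timing could differ by arm.

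The time origin is a smaller matter. Sepsis can be diagnosed before MAP falls below 65 mmHg and before consent. No randomised patient can die in that interval, and day 28 then falls less than 28 days after randomisation.

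**Working it through.** The plan states no figure for 28-day mortality, so there is none to reproduce. Every rate below is an assumption, chosen to show direction and rough size.

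**1. Censoring at discharge, closed form.** Take a constant daily hazard of death in hospital *l*, a constant daily hazard of live discharge *m*, and no deaths after discharge.

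- True 28-day risk = l/(l+m) × (1 − exp(−28(l+m))).
- Kaplan-Meier with discharge censored = 1 − exp(−28 l).

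With l = 0.02 and m = 0.05:

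- True risk: 0.02/0.07 × (1 − exp(−1.96)) = 24.5%.
- Kaplan-Meier: 1 − exp(−0.56) = 42.9%.

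**2. Two arms with different discharge speed, same formulas.**

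| Arm | l | m | True 28-day risk | Kaplan-Meier |
|---|---|---|---|---|
| A | 0.0200 | 0.04 | 27.1% | 42.9% |
| B | 0.0255 | 0.06 | 27.1% | about 51% |
| C | 0.0200 | 0.06 | 22.3% | 42.9% |

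- A against B: true mortality is equal, yet the curves differ by about 8 points against the arm discharged faster. This needs a higher in-hospital death hazard in B (about 0.0255 against 0.020).
- A against C: in-hospital death hazards are equal. The curves coincide and hide a true difference of 27.1 − 22.3 = 4.8 points.

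So the curves can create a difference or conceal one, depending on inputs that the documents do not give.

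**3. Censoring at discharge, simulation over a range.** There were 400,000 patients per scenario. Times of death followed an exponential with scale 8 days, truncated at 28 days. Survivors' discharge times were gamma with shape 2.

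| In-hospital 28-day mortality | Kaplan-Meier, mean 10 days to discharge | Kaplan-Meier, mean 14 days |
|---|---|---|
| 15% | 39% | 25% |
| 22% | 53% | 36% |
| 30% | 65% | 47% |
| 40% | 78% | 60% |

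With 22% mortality in both arms and mean discharge at 9 against 11 days, the curves read 62% against 46%.

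**4. Carrying discharged patients as alive.** Assume 22% die in hospital and 5% of survivors discharged before day 28 die before day 28. With the gamma distribution and a mean of 10 days, 97.6% of survivors leave before day 28.

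- True risk: 0.22 + 0.78 × 0.976 × 0.05 = 25.8%.
- Counted: 22.0%. The upward bias is gone, but 3.8 points of mortality are missed.

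**5. Origin at diagnosis.** The assumptions are a control risk of 22% at 28 days from randomisation, a hazard ratio of 0.7, early-weighted deaths (Weibull shape 0.6), and an exponential delay from diagnosis to randomisation with the same distribution in both arms.

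| Mean delay (days) | Control risk, day 28 from diagnosis | Arm difference from diagnosis | Arm difference from randomisation |
|---|---|---|---|
| 0.5 | 21.7% | 5.9 points | 5.9 points |
| 1 | 21.5% | 6.0 points | 6.1 points |
| 2 | 21.1% | 5.7 points | 5.9 points |
| 3 | 20.5% | 5.7 points | 6.0 points |

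Control risk from randomisation was about 22% throughout. The risk falls slightly because the window after randomisation is shorter, and the arm difference hardly moves.

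**The case against.** The strongest reply is that the document never makes discharge a censoring time. A reader might infer from the Fig 1 legend and the Kaplan-Meier sentence that the mortality estimate is necessarily biased upwards. The documents do not support that: under the other obvious rule the error runs the other way, so even its direction is open. Nor is Kaplan-Meier clearly the tested comparison. *Statistical analyses planned* assigns categorical outcomes to the chi-square or Fisher test, which on its face covers 28-day mortality as a proportion, and it names no log-rank or Cox analysis. These replies stand and limit the point. They do not remove it, because a chi-square test also needs day-28 status for every patient.

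A reader might also infer that starting at diagnosis breaks the randomised comparison. It does not. The interval is over before allocation, so its distribution is the same in both arms in expectation, and the groups are still analysed as randomised. It is also probably short: sepsis must arise in the ICU, study treatment starts when hypotension occurs, urgent inclusion can proceed on oral consent, and the plan counts in dates.

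Finally, an article may leave contact procedures and censoring rules to a fuller document. That is fair for the missing censoring rule. It does not cover the two rules that the article does state: where monitoring for this outcome ends, and where the clock starts.

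**Conclusion.** The point holds in a limited form. Followed as written, the plan does not secure day-28 vital status for patients discharged alive before then, and it does not anchor the 28-day window at randomisation.

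The first matters more. Its effect depends on an unstated rule: overstated and possibly distorted Kaplan-Meier mortality if discharge is a censoring time, or an undercount if discharged patients are taken as alive. In the assumed scenarios the first error is large (22% read as 36% to 53%) and the second is a few points. Neither is a prediction for this trial. The second defect is a matter of alignment: a death-free interval, probably short, that moved the simulated arm difference by at most about 0.3 points.

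Mortality is a secondary outcome for which no power is claimed, and the primary outcome is complete at 6 hours. This should be fixed, but it does not threaten the main result.

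**What to change.** - Record vital status at day 28 after randomisation for every patient, by phone call or record check for those already discharged. Correct the Fig 1 legend to match.
- In *Statistical analyses planned*, count time to death from randomisation.
- State that patients are censored only at day 28 or at true loss to follow-up, never at discharge.
- Report the 28-day risk difference with its 95% confidence interval beside the Kaplan-Meier curves.

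The cost is one check per patient discharged before day 28 and a few changes of wording. For patients already enrolled, the check should be made soon, because status becomes harder to recover with time.
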